## Abstract

**Background:**

Carpal tunnel syndrome (CTS) is the most common neuropathy of the upper limb and a significant contributor to hand functional impairment and disability. Effective treatment options include conservative and surgical interventions, however it is not possible at present to predict the outcome of treatment. The primary aim of this study is to identify which baseline clinical factors predict a good outcome from conservative treatment (by injection) or surgery in patients diagnosed with carpal tunnel syndrome. Secondary aims are to describe the clinical course and progression of CTS, and to describe and predict the UK cost of CTS to the individual, National Health Service (NHS) and society over a two year period.

**Methods/Design:**

In this prospective observational cohort study patients presenting with clinical signs and symptoms typical of CTS and in whom the diagnosis is confirmed by nerve conduction studies are invited to participate. Data on putative predictive factors are collected at baseline and follow-up through patient questionnaires and include standardised measures of symptom severity, hand function, psychological and physical health, comorbidity and quality of life. Resource use and cost over the 2 year period such as prescribed medications, NHS and private healthcare contacts are also collected through patient self-report at 6, 12, 18 and 24 months. The primary outcome used to classify treatment success or failures will be a 5-point global assessment of change. Secondary outcomes include changes in clinical symptoms, functioning, psychological health, quality of life and resource use. A multivariable model of factors which predict outcome and cost will be developed.

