### Aims and objectives

The primary aim of this cohort study is to identify prognostic indicators of outcome for surgical and conservative treatment by corticosteroid injection in patients presenting for nerve conduction tests with symptoms of carpal tunnel syndrome, managed according to current best practice and followed up for up to 2 years.

Specific objectives are:

1) To identify baseline clinical, psychological and sociodemographic predictors for response to treatment by injection and surgical decompression in patients diagnosed with CTS.

2) To describe the course and progression of CTS in treated and untreated patients over 2 years from diagnosis.

3) To describe and identify factors that predict the cost of CTS to the NHS and society over a period of 2 years.

4) To pilot a web-based system for routine collection of clinical baseline and patient-reported outcomes in patients undergoing treatment for CTS.

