### Questionnaire data

Data on putative predictive factors will be collected with a study specific questionnaire through a combination of standardised measures and purposely designed questionnaires:

Symptom severity will be assessed with the 6-item short form of the Boston Carpal Tunnel Questionnaire, the CTS-6 [18].

Hand functional status will be assessed with three subscales of the Michigan Hand Questionnaire (MHQ) which capture unilateral and bilateral hand function, activities of daily living and work performance [19].

Psychological status has been identified as a predictor of outcome in several studies and will be measured using the standardised Hospital Anxiety and Depression scale (HADs) [20].

Health-related quality of life and health utility will be assessed by the EQ-5D-3 L (http://www.EuroQol.org). Results of the EQ-5D-3 L will be converted into utilities by applying UK specific preference weights to the health profiles. QALYs accrued will be calculated by integrating utility with respect to time. QALYs accrued in year two will be discounted by 3.5%.

Comorbidity will be assessed using a self-administered standardised Comorbidity Questionnaire developed by Sangha et al. [21].

Additionally, at baseline other clinical and sociodemographic factors will be collected through self-report including age, sex, ethnicity, work status and type of work, smoking status, alcohol use, household income.

Results from NCS will be requested from the neurophysiologist once patients have consented and been enrolled into the study. Median nerve sensory nerve action potential (amplitude and velocity) for digit III and distal motor latency (amplitude and velocity) will be recorded. Padua’s criteria [17,22] for classifying CTS severity according to the neurophysiology results will be used to grade severity from 1 to 6 (mild to extremely severe).

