### Outcomes

The primary outcome used to classify treatment successes and failures will be patient-reported global assessment of outcome (GAO) at 2 years using a 5 point ordinal scale: worse = 1, unchanged = 2, slightly better = 3, much better = 4, completely cured = 5. A grade of 3 or above will be defined as treatment success. Secondary outcomes include patient-reported clinical symptoms (CTS-6), functioning (MHQ), psychological health HADs, quality of life (EQ-5D) and resource use.

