### Analysis

The primary outcome (global assessment of outcome) will be modelled using a binary logistic regression model. Predictors will be considered on a univariate basis and those found to have a statistically significant effect on the outcome (at the 10% level) will be entered simultaneously into a multivariable model. A backwards deletion approach based upon change in likelihood will be used to remove those predictors with no significant independent effect. An ordinal logistic regression model will also be considered based upon the proportional odds assumption using the original 5 point ordinal scale as the outcome. However, as the assumption is often difficult to verify, this will be considered as a secondary analysis.

Secondary outcomes will be analysed in a similar fashion using regression models with link functions and error terms appropriate to the distribution of the outcome of interest.

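### If the secondary scale outcomes are modelled as changes, own-baseline coefficients are contaminated and the 10% screen can keep or drop the wrong predictors; own baseline should be in every model

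*Protocol article*

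**What the plan says.** The protocol article describes the secondary outcomes twice. The Abstract (Methods/Design) says "Secondary outcomes include changes in clinical symptoms, functioning, psychological health, quality of life and resource use". The Outcomes section says "Secondary outcomes include patient-reported clinical symptoms (CTS-6), functioning (MHQ), psychological health HADs, quality of life (EQ-5D) and resource use", which names the scales but not a change in them. Neither gives a formula, and neither fixes the time point for these scales.

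The same instruments supply candidate predictors. The Questionnaire data section opens with "Data on putative predictive factors will be collected with a study specific questionnaire through a combination of standardised measures and purposely designed questionnaires" and then lists CTS-6, MHQ, HADs and EQ-5D among them. The first specific objective is "To identify baseline clinical, psychological and sociodemographic predictors for response to treatment by injection and surgical decompression in patients diagnosed with CTS".

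The Analysis section fixes the selection method. Each predictor is first tested alone for a "statistically significant effect on the outcome (at the 10% level"); those that pass enter a multivariable model together, followed by backward deletion. For the secondary outcomes it says "Secondary outcomes will be analysed in a similar fashion using regression models with link functions and error terms appropriate to the distribution of the outcome". It does not say whether the response is the follow-up score or the change, or whether the baseline value of the same scale is always kept.

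**The concern.** When the response is follow-up minus baseline, the baseline score appears on both sides. Measurement error and ordinary fluctuation at entry then make patients who score badly at baseline improve more on average, whatever their prognosis. A predictor that correlates with baseline severity (for example nerve conduction grade, or HADs when the response is CTS-6) picks up part of this when tested alone.

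Two things are at stake. First, the coefficient of own baseline cannot be read as prognostic, and its sign can depend on which of the two outcome descriptions is followed. The Discussion cites a surgical study and an injection study in which greater baseline severity or functional limitation went with a worse outcome. A finding that severe patients improve more could look like a contradiction when it is partly a product of the response chosen. Second, the screen can admit predictors with no independent effect and reject predictors that have one. A predictor rejected at the screen never reaches the multivariable model.

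**Working it through.** **The plan's own figure.** The document gives no figure for the secondary outcomes. Its only calculation is the power for the primary outcome (Sample size section). Wald power for a binary predictor is Φ(ln OR·√(N/V) − 1.96), with V = 1/[0.5·p0(1−p0)] + 1/[0.5·p1(1−p1)]. I assume two-sided alpha of 0.05 and 33% as the success rate in the reference group.
- N = 1070, OR 1.51: p1 = 0.427, V ≈ 17.22, and 0.412 × 7.88 − 1.96 ≈ 1.29, so power is 90.1%.
- N = 535, OR 1.79: p1 = 0.469, V ≈ 17.08, and 0.582 × 5.60 − 1.96 ≈ 1.30, so power is 90.3%.

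Both agree with the stated 90%. The two sample sizes are used below.

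**Inputs that the document does not give (all assumed).** Baseline to follow-up correlation r of 0.3 to 0.9; equal SDs at both times; scale reliability of 0.7 to 0.9; SD of true change of 0.5 to 1.0 baseline SDs; a correlation of 0.3 between another predictor and baseline. Scores are in SD units, with higher meaning worse.

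**Step 1: own baseline.** With equal SDs, the slope of the follow-up score on baseline is r. The slope of change on baseline is r − 1, and the correlation of change with baseline is −√((1−r)/2).

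| r | slope, follow-up score | slope, change | correlation with change |
|---|---|---|---|
| 0.3 | +0.30 | −0.70 | −0.59 |
| 0.5 | +0.50 | −0.50 | −0.50 |
| 0.7 | +0.70 | −0.30 | −0.39 |
| 0.8 | +0.80 | −0.20 | −0.32 |
| 0.9 | +0.90 | −0.10 | −0.22 |

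In simulation, baseline passed the 10% screen on change in all 1,000 runs for every r, at both N = 1070 and N = 535.

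**Step 2: how much of that is artefact.** Step 1 gives the whole association, real and spurious together. To isolate the artefact, let true change be independent of true baseline and let the scale have reliability ρ. The slope of change on observed baseline is then −(1−ρ): −0.30, −0.20 and −0.10 for ρ = 0.7, 0.8 and 0.9. With s the SD of true change, the share of variance explained is (1−ρ)²/[s² + 2(1−ρ)].
- Largest case (ρ = 0.7, s = 0.5): 0.09/0.85 = 0.106.
- Smallest case (ρ = 0.9, s = 1.0): 0.01/1.20 = 0.008.

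The artefact alone thus explains about 1% to 11% of the variance in change. It still carries baseline through the screen in 92–100% of runs at N = 1070 and 68–100% at N = 535.

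**Step 3: other predictors at the screen.** Let F = 0.5·B + g·X + error (error variance 0.75), with B and X standardised and correlated 0.3.
- *No independent effect (g = 0).* The covariance of X with change is (0.5 − 1) × 0.3 = −0.15. The variance of change is 2(1 − 0.5) = 1, so the correlation is −0.15. At N = 535, 0.15·√535/√(1 − 0.0225) = 3.51, and Φ(3.51 − 1.645) = 0.97. Simulation gives 97% at N = 535 and 100% at N = 1070. With own baseline in the screening model the rate is about 10%, the nominal level.
- *Real worsening effect (g = 0.15).* The covariance with change is −0.15 + 0.15 = 0. The predictor passes in about 10% of runs at either N, which is chance. With own baseline in the screening model it passes in 98% (N = 535) to 100% (N = 1070).

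Replacing change by the follow-up score is not enough by itself. For g = 0 the correlation becomes +0.15, and the unadjusted screen still passes X in about 98% of runs at N = 535, now with the opposite sign. What corrects the screen is having own baseline in the model.

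**Step 4: the multivariable model.** With own baseline included, change = F − B has the same coefficients as F for every other predictor; only the baseline coefficient moves, by exactly 1. A simulated dataset gave −0.062 for the other predictor under both responses, and +0.432 against −0.568 for baseline.

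**The case against.** The strongest reply is that the document never commits to a change-score model. The Abstract speaks of change in broad domains and names no scale. The Outcomes section, which is where outcomes are defined, names the scales and does not mention change. The Abstract's phrase also covers resource use, which the cost analysis totals over two years and does not difference from baseline, so the word may be loose or may point to the descriptive course objective. The choice of response and the handling of own baseline are details that an analysis plan often settles. This stands to the extent that the response variable is unfixed here, not fixed as change. It does not dispose of the point: the two descriptions differ, and the one-at-a-time screen, which leaves out own baseline when any other predictor is tested, is stated method and not silence.

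The second reply is that the plan largely repairs itself. If own baseline passes the screen and stays in the multivariable model, the other coefficients equal those under the fix. That is correct (Step 4). It does not help a predictor already lost at the screen, and nothing guarantees that own baseline is kept through backward deletion.

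A reader might infer more: that the scale outcomes are defined as changes, that baseline severity will predict improvement through regression to the mean alone, and that 15% to 35% of the variance in change is artefact. The documents do not support this. The first part joins the Abstract's wording to scale names from another section. The percentages are (1−r)/2 for r = 0.7 to 0.3, which counts the entire baseline-change association as spurious, although r below 1 also reflects real differences in course.

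**Conclusion.** The concern holds conditionally. The two descriptions of the secondary outcomes differ, and the stated screen omits own baseline. If change is modelled, as the Abstract's wording suggests, the own-baseline coefficient is contaminated by mathematical coupling and regression to the mean: its slope is r − 1 in place of +r. A real association between baseline and course may coexist with this. Predictors correlated with baseline can be wrongly kept (about 97% at N = 535 in the worked case) or wrongly dropped (passing only at the chance rate of about 10%).

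These sizes rest on assumed r, equal SDs, reliabilities and predictor correlations, none of which the document gives; the zero covariance in the wrongly dropped case comes from choosing an effect that exactly offsets the coupling. Coefficients of other predictors are unaffected once own baseline is in the multivariable model. The primary outcome is a patient's global rating at 2 years, not a difference between scale scores, and is not affected. The point is a worthwhile improvement to the secondary analyses and does not threaten the study's main result.

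**What to change.** 1. Make the Abstract and the Outcomes section agree on the secondary outcomes.
2. State that each scale outcome (CTS-6, MHQ, HADs, EQ-5D) is analysed as the follow-up score at a named time point.
3. Force the baseline value of the same scale into every model for that outcome: the one-at-a-time screen, the multivariable model and every step of backward deletion. Interpret the other predictors conditional on it.
4. State that the coefficient of baseline on its own change will not be read as prognostic.
5. Keep change scores for description, under the course and progression objective.

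The cost is wording in the outcome definition and the model specification. The baseline questionnaires are already planned, so there are no new data and no extra patients.

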**Discussion:**

This prospective cohort study will provide important data on the clinical course and UK costs of CTS over a two-year period and begin to identify predictive factors for treatment success from conservative and surgical interventions.

## Background

Carpal Tunnel Syndrome (CTS) is the commonest peripheral entrapment neuropathy which causes pain, tingling, numbness and weakness in the distribution of the median nerve of the hand. It is bilateral in 55-65% of cases [1] and is a significant contributor to impaired hand function and work disability. In the UK in 2000 the annual age standardised rate per 100,000 was 87.8 for men and 192.8 for women [2]. There are no estimates of the cost of CTS to UK society or the NHS, however societal costs to the USA of patients undergoing decompression surgery were estimated at over $2bn in 1995 [3]. More recently in 2007, the income loss per CTS patient over a period of 6 years was estimated at $45,000-89,000 compared with controls (upper extremity fracture and dermatitis) [4].

Treatment options which are supported by high quality evidence are corticosteroid injection for mild to moderate symptoms [5,6] and surgical decompression in moderate to severe cases [7]. Surgery rates in 1995 in the UK were 71 per 100,000 [8] and rising to 90/100,000 a decade later [9]. Although steroid injection is an effective and relatively safe first line of treatment, its benefit beyond 8 weeks has not been demonstrated [5]. A UK study by Latinovic found that 31% of patients proceeded to surgery within 1 year of initial presentation to their General Practitioner [2]. A study in the Netherlands found that only 25% of patients had a good outcome at 1 year after steroid injection [10]. Similarly, Meys et al. [11] reported that 67% of patients treated by injection required surgery by 1 year. Surgical rates vary from country to country and depend on referral criteria. The introduction of 'low priority procedure’ thresholds by NHS trusts in England may account for lower surgery rates in the UK compared to the US or Europe.

The treatment algorithm currently used by most NHS Trusts in England is to refer patients to surgery only when symptoms are severe and disabling or when steroid injections have failed. Where injection fails to resolve symptoms, this prolongs the duration of symptoms and associated disability as well as incurring direct and indirect costs. As yet it is not possible to predict which patients will obtain long-term relief from steroid injection and which will require surgical decompression. Longer duration of symptoms and greater severity of symptoms are also associated with poorer surgical outcomes although the evidence seems equivocal [12].

Surgical decompression is effective in most patients, however reported success rates vary. An analysis of pooled results from 209 studies, representing 32,936 operations, found that 75% of patients considered themselves improved, much better or cured [13]. Misdiagnosis and surgical errors such as incomplete decompression are the most common reasons for failure. The answer to the question of what factors predict a good surgical outcome has so far eluded us.

The authors of a recent systematic review of surgical and non-surgical treatments concluded that future research needed to focus on 'prognostic studies which lead to better patient characterisation and the identification of predictive factors that indicate likely response to specific treatments’ [14]. Although a number of studies have explored prognostic factors, these have been conducted either retrospectively or in the context of randomised trials which has limitations [15]. To date no prospective cohort study of prognostic factors has been undertaken. The value of high quality prognostic research is that it leads to a better understanding of disease progression, better targeting of effective treatments that mitigate progression and allows more reliable information about the risk of a negative outcome to be communicated to patients [15]. A cohort study of prognostic factors would be the first necessary step towards the development and further external validation of clinical prediction rules. This work would also address the need to focus on outcomes that matter to patients as outlined in the NHS Outcomes Framework [16] by collecting patient-reported outcomes on one of the commonest elective surgical procedures in the upper extremity.

### Aims and objectives

The primary aim of this cohort study is to identify prognostic indicators of outcome for surgical and conservative treatment by corticosteroid injection in patients presenting for nerve conduction tests with symptoms of carpal tunnel syndrome, managed according to current best practice and followed up for up to 2 years.

Specific objectives are:

1) To identify baseline clinical, psychological and sociodemographic predictors for response to treatment by injection and surgical decompression in patients diagnosed with CTS.

2) To describe the course and progression of CTS in treated and untreated patients over 2 years from diagnosis.

3) To describe and identify factors that predict the cost of CTS to the NHS and society over a period of 2 years.

4) To pilot a web-based system for routine collection of clinical baseline and patient-reported outcomes in patients undergoing treatment for CTS.

## Methods/Design

### Design

A prospective observational cohort study of patients diagnosed with CTS through clinical examination and history and confirmed by nerve conduction studies. Data on putative prognostic factors and outcomes of corticosteroid injection and surgery for CTS will be collected over a 2 year period.

### Study setting

In Norfolk approximately 1200 patients per annum are referred with suspected carpal tunnel syndrome to clinical neurophysiology at the Norfolk and Norwich University Hospitals NHS Foundation Trust (NNUH). Nerve conduction studies (NCS) are done on both hands to confirm a clinical diagnosis, objectively grade the severity of compression and make treatment recommendations based upon it. Referrals come from primary care e.g. general practitioner, community physiotherapist, and secondary care e.g. orthopaedics, rheumatology and plastic surgery.

### Inclusion criteria

Adults aged 18 years and over who attend for NCS in the Department of Neurophysiology and are confirmed to have CTS of at least mild severity (grade ≥ 1 on Padua scale [17]) based on a combination of NCS results and clinical diagnosis, in at least one hand and for which either no treatment is recommended at present or conservative or surgical treatment is recommended. Patients with idiopathic as well as secondary CTS due to diabetes or hypothyroidism will be included.

### Exclusion criteria

•Patients with unilateral CTS who have had carpal tunnel surgery in that hand in the last 12 months.

•Pregnancy and up to and including 12 months postpartum due to the often transient nature of CTS.

•Serious co-morbidity e.g. malignancy, severe mental illness and where the GP considers the patient to be vulnerable and for whom participation would be otherwise detrimental.

•Other symptomatic upper limb mononeuropathies, vibration induced conditions, radiculopathy or thoracic outlet syndrome.

•Any other sensory or motor disturbances affecting the upper limb such as stroke, multiple sclerosis, nerve injury.

•Unable to read or write English.

### Recruitment procedure

Potentially eligible patients will be identified by the consultant neurophysiologist based on the clinical history and NCS results. The patients will be informed verbally about the current study and given an information pack containing an invitation to participate, a screening questionnaire and consent form. Patients will be asked to read through these in their own time at home and a telephone number for the study coordinator is provided if patients have any further questions. Patients who wish to participate will be asked to complete and return the consent form and screening questionnaire in an enclosed stamped addressed envelope within 2 weeks. Those who do not wish to participate will be asked to still complete the screening questionnaire which does not require disclosure of any personally identifiable information. Their data will be used to compare the consenters with non-consenters and assess external validity of the study. Those patients returning a valid signed consent form will be contacted by the study coordinator via the telephone who will verify that they meet eligibility criteria and also to verify that patients have given fully informed consent. In order to maximise response rates a reminder letter will be sent by the consultant neurophysiologists to all patients who were deemed eligible and given a study invitation pack within 1 week of attendance at the department of Neurophysiology. Each patient will only be enrolled into the study once even where CTS presents bilaterally.

